#### ​Adverse events

Foreseeable adverse events (AE) occurring as a result of the trial intervention(s) will be recorded. Participants will receive information on the potential AEs resulting from the treatment exercises and what they should do if they experience an AE, as would happen as part of standard NHS procedures.

Expected general side effects of any exercise, such as delayed-onset muscle soreness and temporary increases in pain <1 week, will not be recorded as AEs. Pain increases >1 week will be recorded in patient-reported questionnaires. Although unlikely, any exacerbations of other medical conditions during exercise or exercise-related injurious falls will be recorded in patient-reported questionnaires or by the site investigators if they become aware of such an event.

A serious AE (SAE) is any unexpected untoward medical occurrence related to the trial interventions that results in death, is life-threatening, requires inpatient hospitalisation or prolongation of existing hospitalisation, or results in persistent or significant disability/incapacity. SAEs are likely to be rare and are unlikely to occur as a result of the exercise programmes delivered in this study. If an SAE arises between study enrolment and final follow-up visit and is deemed related to the trial interventions, the Clinical Trials Unit standard operating procedures will apply.

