### Interventions

#### ​Training and monitoring of intervention delivery

The best-practice advice and progressive functional exercise interventions will be provided face-to-face and one-to-one by physiotherapists. The study team will give the treating therapists training and an intervention manual on the theory and practical delivery of the interventions. Treating physiotherapists will record the delivery and content of the sessions attended by each participant.

Patient pathways vary at different hospitals so patients may have had instruction on basic ankle exercises, wound care and use of walking aids from a physiotherapist or other health professional while an inpatient or in an acute fracture clinic before starting the study interventions. This will be recorded in the study treatment log. The intervention session(s) can be tailored to the patient’s recovery level, as per usual care. Some centres make referrals for physiotherapy while patients are inpatients or at earlier clinic follow-ups. Other centres delay referrals until a clinic review several weeks later. The study will adapt screening and recruitment to embed in the patient pathway as much as is practical. The process at each centre will be reviewed as the study progresses.

The best-practice advice or progressive functional exercise sessions will be given when the participant can mobilise with unrestricted weight-bearing and do ankle exercises as guided by their surgeon or physiotherapist. We anticipate that this will usually be around 6 to 8 weeks post-injury.

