Healthcare use	NHS outpatient and community services (eg, general practitioner, additional physical therapy) NHS inpatient and day case (eg, radiography, readmissions) Private healthcare services	3 and 6 months
Out-of-pocket expenses	Patient-related out-of-pocket expenses recording form	3 and 6 months
Adverse events	Patient-reported adverse events	3 and 6 months

NHS, National Health Service.

Patient-reported outcomes at 3 and 6 months will be:

ankle-related symptoms and function: Olerud and Molander Ankle Score^38^
lower-limb function limitations: Lower Extremity Functional Scale^39^
pain: Visual Analogue Scale, 0 to 100 scale health-related quality of life: EQ-5D-5L score^40^
fear of falls: Falls Efficacy Scale-International (short version)^41^
self-efficacy: self-efficacy exercise score^42^
return to desired activities, including work, social life and sport activitieswalking aid use and distancesexercise adherence

At 6 month follow-up, a blinded outcome assessor will collect objective measures of ankle function and physical performance:

ankle joint range: hand-held goniometry^43^
muscle strength: hand-held dynamometry (Lafayette Manual Muscle Test System, Lafayette Instrument, Indiana, USA) of ankle dorsi/plantarflexion using a ‘make’ approach (working up to a maximal contraction over a maximum of 5 s and without pushing into pain and the assessor maintaining position of the device).^44^ Participants will be measured three times and have at least 10 s rest between attempts. Self-reported body weight will be recorded to aid interpretation of strength measures.mobility and balance: short physical performance battery.^45^ The test involves physical tests of balance, walking speed and repeated rises from a chair. It has been used extensively in clinical trials owing to its practical utility, the strong evidence base for its measurement properties, and its relationship to frailty, risk of falls and disability in older adults.^46^

Data on health resource use (consultation with primary and secondary care, prescribed and over-the-counter medication use, additional physiotherapy and hospital admission), additional out-of-pocket expenses and work absence (number of sickness days) will also be collected to inform a future definitive RCT. A full health economic evaluation will not be conducted. Data will be collected alongside the other outcome measures in participant questionnaires.

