#### ​Statistical analysis

Feasibility outcomes will be reported, including the number of participants who are approached, are eligible, consent to randomisation and are followed-up, attendance of intervention sessions, completion rates of exercise diaries and data completeness. Baseline characteristics will be reported using descriptive statistics, per group and overall, using mean and SD (or median and IQR if non-normally distributed), and minimum and maximum, for continuous variables and number and percentage of patients in each group for binary or categorical variables.

Clinical outcome measures will be reported descriptively. Differences between treatments for the intention-to-treat population will be reported with 95% CIs. Withdrawals from treatment and the trial will be reported, with reasons where provided. AEs, and SAEs will be reported, both the number of participants that experience an event and the total number.

The primary statistical analysis will be carried out on the basis of intention-to-treat, with all randomised participants included and analysed according to their allocated treatment group, irrespective of which treatment they actually receive or their treatment compliance.

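### As worded, the adverse event rules give no category to an intervention-related harm that is both unforeseen and non-serious

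*Protocol article*

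**What the plan says.** The Adverse events section opens with the recording rule: "Foreseeable adverse events (AE) occurring as a result of the trial intervention(s) will be recorded". It then makes one exclusion: "Expected general side effects of any exercise, such as delayed-onset muscle soreness and temporary increases in pain <1 week, will not be recorded as AEs". After that it names what is captured. On pain: "Pain increases >1 week will be recorded in patient-reported questionnaires". On other harms: "any exacerbations of other medical conditions during exercise or exercise-related injurious falls will be recorded in patient-reported questionnaires or by the site investigators", the investigator route applying when the site becomes aware of such an event.

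The definition of a serious event begins "A serious AE (SAE) is any unexpected untoward medical occurrence related to the trial interventions that results in death, is life-threatening" and continues with hospital admission or prolonged stay and lasting disability. It has three conditions: unexpected, related and serious.

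Two other places bear on the point. Table 2, under Outcomes, has a row "Patient-reported adverse events" at 3 and 6 months, with no definition and no restriction. Statistical analysis promises a summary: "AEs, and SAEs will be reported, both the number of participants that experience an event and the total number".

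**The concern.** Foreseeability is used here as a condition for recording an event, when it is normally a property assigned to an event after it has been recorded. A rule of that kind is weakest for the harms that nobody listed in advance, and a pilot should be able to bring those to light. The article calls progressive functional exercise a novel approach. Sessions begin once the participant can bear weight without restriction and exercise the ankle as guided by the surgeon or physiotherapist. On timing the article says: "We anticipate that this will usually be around 6 to 8 weeks post-injury".

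At stake is the completeness of the adverse event totals that the pilot will report and that planners of a definitive trial will read. The article also does not define foreseeable, so whether a given event is recorded could depend on who is judging it.

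**Working it through.** The article states no figure on this point, so the check is of wording. Take events related to the intervention, classify them by whether they were foreseen and whether they are serious, and apply the two rules in the Adverse events section.

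1. **Foreseeable, non-serious.** Inside the recording rule, apart from the excluded general effects of exercise. Recorded as an adverse event.
2. **Unforeseen, serious.** Meets all three conditions of the serious event definition. Recorded as a serious adverse event.
3. **Unforeseen, non-serious.** Fails the recording rule because it was not foreseeable. Fails the serious event definition because no seriousness criterion is met. Neither rule applies.
4. **Foreseeable, serious.** Fails the serious event definition, which requires the event to be unexpected, and so falls back to the ordinary adverse event rule. This is a side effect of the same drafting and not the point made here.

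Cell 3 is the gap. Does any other text fill it?

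- The events named in the section (prolonged pain, exacerbation of other conditions during exercise, injurious falls during exercise) are themselves anticipated. They catch an unforeseen problem only if it shows itself in one of those forms.
- The Table 2 row has no qualifier, so a participant could report such an event there. The row does not define an adverse event; only the Adverse events section does.
- Statistical analysis counts adverse events and serious adverse events without redefining either, so it takes over whatever the definitions admit.
- Treatment logs (Feasibility criteria) monitor tolerability, and follow-up questionnaires (Concomitant care) record additional treatments and contacts. Neither is named as a source for the adverse event totals.

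No passage assigns cell 3 to the reported totals.

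**Illustration of scale.** Inputs: the minimum target of 48 (Sample size) and 1:1 allocation (Randomisation) give 48 / 2 = 24 per arm. The incidence p is an assumption, because the article gives none. The chance of at least one affected participant in an arm is 1 − (1 − p)^24.

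- p = 5%: 1 − 0.95^24 = 1 − 0.29 = 0.71
- p = 10%: 1 − 0.90^24 = 1 − 0.08 = 0.92

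These figures show only that events of this frequency would probably occur in a pilot of this size. They say nothing about how many would be missed.

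**The case against.** The strongest case on the other side is that this is loose wording with little practical effect. The recording sentence does not say that only foreseeable events are recorded. The Table 2 row and the analysis sentence are both unqualified. The prolonged pain item is not tied to any cause, so it would catch many problems at the injured ankle that show as pain. Treatment logs, reasons for withdrawal where given, participant interviews and the therapist focus group are further ways for an unexpected problem to come to notice. This is also a condensed article, and the questionnaire, which may already contain an open question, is not shown.

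Much of this stands, and it rules out two stronger readings. A reader might infer that the recorded count of unforeseen non-serious harms must be zero whatever their true frequency. That does not follow, because the unqualified patient-reported item could pick them up. A reader might also infer that wound, metalwork or delayed-healing problems are the harms being lost. The documents do not support that either. In a trial that enrols surgically fixed fractures and excludes certain wounds and external fixation, such problems are arguably foreseeable, and if caused by the intervention they would fall inside the recording rule.

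The objection does not remove the gap itself. The word foreseeable has no function unless it restricts. The other routes are not described as feeding the adverse event counts. The restriction is stated in the article, so it is not a detail left to a fuller document.

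**Conclusion.** The point holds as a defect of definition. An unforeseen, non-serious, intervention-related event meets neither the adverse event rule nor the serious event definition. The Table 2 item might collect it, but nothing says that it enters the reported totals. The totals may therefore understate harm, by an amount that cannot be estimated from the document.

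The conclusion rests on reading the recording sentence as restrictive and on the Adverse events section being the only definition given. It does not depend on the assumed incidences of 5% and 10%, or on any particular clinical example. It touches none of the four success criteria and no input to the sample size. It is still worth correcting, because the change is small and the pilot is meant to inform a larger trial.

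**What to change.** - Delete the word foreseeable from the recording rule, so that any untoward event is recorded in both arms whether or not it was anticipated. Keep the stated exclusion of expected general effects of exercise.
- Make sure the existing patient-reported adverse event item at 3 and 6 months includes an open question on any other problem. If the questionnaire already has one, say so in the Adverse events section, so that the text and Table 2 agree.
- Code expectedness and relatedness afterwards as separate fields. Relatedness then no longer decides what is recorded, and intervention-related events can still be tabulated on their own.
- Under Statistical analysis, report participants with an event and total events by arm, with those two fields shown.

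The cost is a reworded paragraph, at most one added question, more minor events to code, and adverse event counts somewhat higher than under the present wording. Visits, follow-up times and sample size are unchanged.

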## Methods and analysis

### Study design

A multicentre pilot RCT with an embedded qualitative study. Participants will be allocated to either: (i) best-practice advice (one session of face-to-face advice delivered by a physiotherapist, with up to two further optional advice sessions) or (ii) progressive functional exercise (up to six sessions of individual face-to-face physiotherapy) (see figure 1).

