#### ​Progressive functional exercise

Participants will undertake progressive functional resistance training and balance exercises. A physiotherapist will instruct on, supervise and progress the exercises in up to six sessions over 16 weeks. This period allows sufficient time for neuromuscular adaptation to exercise.^28^ The programme can end early if all rehabilitation goals are achieved in under six sessions. The first session will be 20 to 60 min and the rest up to 30 min, consistent with physiotherapy sessions in the NHS. Physiotherapists will provide assessment, advice, education about progressing recovery, gait training, walking aid instruction and an information booklet.

The programme will be highly structured but calibrated for each individual. Tailoring programmes to the participant is a key feature of effective interventions in older adults.^29^ All participants will receive a core set of functional lower limb strengthening exercises in line with the evidence for improving muscular strength and power in older persons’ rehabilitation.^30^ Strength improvements do not necessarily translate to function and balance improvements. The programme will include supervised gait training to target major walking difficulties after ankle fracture. Gait training improves motor control during walking in older adults, which is related to functional mobility and balance improvements.^31^ Balance exercises will also be included in the programme and introduced once the participant is able to weight bear sufficiently to perform these. Exercises will be practised in the clinic but conducted at home to achieve an effective dose. Based on the participant’s functional goals, exercises will be progressed to make them task-specific, for example walking on uneven surfaces or slopes, climbing stairs or jogging. The participants will receive a personal exercise guide and diary. Exercise progression will be based on evidence-based guidelines^24^ but individualised by progressing and regressing the volume and load in line with each participant’s capabilities and preferences.

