### Outcome measures

#### ​Feasibility criteria

The main aim of this pilot RCT is to determine the feasibility of a future definitive trial.^37^ The focus will not be on a primary outcome of effectiveness, but instead on meeting success criteria. The main uncertainty is whether patients find it acceptable to be randomised to different types of physiotherapy. Screening data from the AIM trial gives confidence that there are enough potential participants to investigate the feasibility criteria. To determine the feasibility of a definitive RCT, the success criteria are:

A study participation rate of at least 25% of those eligible, to indicate acceptability and generalisability.At least 48 eligible participants across at least three sites agree to participate over a maximum of 18 months.At least 85% of participants complete the study intervention sessions.At least 80% of participants attend study follow-up at 6 months.

Descriptions from the participant interviews and therapist focus group that indicate randomisation/interventions are acceptable will also be used to assess feasibility. Treatment logs will monitor intervention fidelity and tolerability. Adherence to home exercise will be monitored via participant self-reports. An estimate of SD for the primary outcome is not required as the AIM trial will provide this information for the definitive trial.

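### Some adverse events can also be noted passively by sites, contact differs by arm, and counts are not split by source, so counts of these events may be inflated in the exercise arm

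*Protocol article*

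**What the plan says.** All places are in the protocol article.

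- **Scope (Adverse events).** "Foreseeable adverse events (AE) occurring as a result of the trial intervention(s) will be recorded".
- **Common route (Outcomes, Table 2).** The row for adverse events reads "Patient-reported adverse events 3 and 6 months". Both arms are on this schedule.
- **Additional route (Adverse events).** Flare-ups of another medical condition during exercise, and injurious falls linked to exercise, "will be recorded in patient-reported questionnaires or by the site investigators if they become aware of such an event".
- **Pain.** "Pain increases >1 week will be recorded in patient-reported questionnaires". No site route is stated for it.
- **Contact, exercise arm (Progressive functional exercise).** A physiotherapist will instruct on, "supervise and progress the exercises in up to six sessions over 16 weeks". The programme may stop sooner if goals are met.
- **Contact, advice arm (Study design).** "one session of face-to-face advice delivered by a physiotherapist, with up to two further optional advice sessions". The Best-practice advice section makes the optional sessions telephone-only later in recruitment.
- **Reporting (Statistical analysis).** "AEs, and SAEs will be reported, both the number of participants that experience an event and the total number". Source is not mentioned.
- **Tolerability (Feasibility criteria).** "Treatment logs will monitor intervention fidelity and tolerability".

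**The concern.** A count of recorded events reflects how often events happen and how likely each one is to be noticed. The questionnaires give both arms the same opportunity at the same times. The site route does not: it has no fixed timing or common prompt, and a site seeing a participant up to six times has more occasions to hear of a fall than one seeing the participant once. Treating physiotherapists also know the allocation (Blinding), and the scope of recording calls for a judgement that the event resulted from the intervention.

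If events from both routes go into one count, a reader who sets the arms side by side cannot tell a difference in harm from a difference in observation. Because the Outcomes section says outcomes are collected to learn whether they can be collected in a definitive trial, the greater risk is that this way of counting is carried forward into that trial.

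**Working it through.** The plan states no adverse-event rate, precision or power, so there is no figure to reproduce. The check asks in which direction, and over what range, unequal contact could move the counts.

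**Inputs from the protocol article**
- Sessions: exercise up to 6; advice 1, or 3 if both optional sessions are taken (1 + 2).
- Sample: minimum 48, allocated 1:1, so 48 / 2 = 24 per arm.

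**Assumptions (not in the document)**
- Equal true risk in both arms, to isolate the effect of capture.
- q = probability that the questionnaires capture an event, equal in both arms.
- s = probability that any one session brings to light an event the questionnaires miss.

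**Formula.** With k sessions, P(recorded) = 1 − (1 − q)(1 − s)^k. The apparent ratio is P at k = 6 divided by P at k = 1 or k = 3.

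| q | s | Exercise, k = 6 | Advice, k = 1 | Ratio | Advice, k = 3 | Ratio |
|---|---|---|---|---|---|---|
| 0.8 | 0.02 | 0.823 | 0.804 | 1.02 | 0.812 | 1.01 |
| 0.8 | 0.10 | 0.894 | 0.820 | 1.09 | 0.854 | 1.05 |
| 0.7 | 0.20 | 0.921 | 0.760 | 1.21 | 0.846 | 1.09 |
| 0.5 | 0.20 | 0.869 | 0.600 | 1.45 | 0.744 | 1.17 |

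Last row written out: 1 − 0.5 × 0.8^6 = 1 − 0.5 × 0.262 = 0.869; 1 − 0.5 × 0.8 = 0.600; 0.869 / 0.600 = 1.45.

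**Counting return sessions only.** The first session can reveal little that happened after the programme began, so 5 against 0 or 2 return sessions is an alternative. Take q = 0.60.
- s = 0.10: exercise 0.60 + 0.40 × (1 − 0.9^5) = 0.764. Against 0.60 the ratio is 1.27; against 0.60 + 0.40 × (1 − 0.9^2) = 0.676 it is 1.13.
- s = 0.20: exercise 0.60 + 0.40 × (1 − 0.8^5) = 0.869. Against 0.60 the ratio is 1.45; against 0.60 + 0.40 × (1 − 0.8^2) = 0.744 it is 1.17.

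**Limits.** If s = 0 or q = 1, the ratio is 1.00. Whenever s > 0 and q < 1, it exceeds 1 in the direction of the exercise arm.

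**In participants.** At an assumed true risk of 10%, the largest gap in the table is 24 × 0.10 × 0.869 = 2.09 against 24 × 0.10 × 0.600 = 1.44, a difference of 0.65 of a participant.

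**After the fix.** Counting from the common questionnaires alone sets s = 0, so the contact-driven ratio is 1.00 for every q, provided q is the same in both arms.

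**The case against.** The case on the other side is substantial, and much of it stands.

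- **The site route is narrow.** It is stated for two kinds of event, which the protocol calls unlikely. Table 2 defines the outcome as patient-reported. This stands, and it confines the point to those events.
- **The text names site investigators, not treating physiotherapists.** Nothing says that physiotherapists report adverse events at each session. This stands: the link from sessions to site awareness is an inference. It is a reasonable one, since sessions are an obvious way for a site to learn of an event.
- **Contact is not always six against one.** Exercise can end early, advice participants can take two more sessions, a telephone call is still a contact, and both arms have a 6-month hospital visit. This reduces the imbalance without removing it.
- **The events counted are those caused by the intervention.** More supervised exercise could produce more of them, so a higher count need not be an artefact. This stands. Splitting by source would help a reader weigh the two explanations.
- **No safety test and no adverse-event success criterion are planned.** The sentence on confidence intervals follows the one on clinical outcome measures, and the protocol ties refinement of the interventions to the qualitative study. This stands, and it limits the effect on the pilot's own conclusions.
- **Tabulation by source is usually left to the analysis plan.** That is fair for table layout. However, the unequal capture route and the unseparated count are both stated in the protocol article itself.

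**Conclusion.** The point holds as a risk: as written, counts of exacerbations and exercise-related injurious falls may be inflated in the exercise arm. The direction follows if sessions bring to light any event that the questionnaires miss. The size cannot be determined from the document. The ratios of about 1.0 to 1.45 rest wholly on assumed capture rates and on the sessions actually taken, and with 24 per arm and an assumed 10% risk they amount to less than one participant.

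A reader might infer that the reported adverse-event counts as a whole are biased against exercise, or that a planned safety comparison is invalid. The documents support neither. The same questionnaires cover both arms, pain increases over 1 week have only that route stated, and no formal safety comparison is specified. Nor does the protocol specify a between-arm contrast of tolerability from the treatment logs. The point is modest for this pilot and matters more if the method passes unchanged to the definitive trial.

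**What to change.** Amend the Adverse events and Statistical analysis sections as follows.

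1. Record the source of each adverse event (3-month questionnaire, 6-month questionnaire or site).
2. Make any between-arm comparison, of participants and of events, on those reported in the common 3- and 6-month questionnaires, and show the number of questionnaires returned as the denominator.
3. Report site-noted events separately by arm, alongside the number of sessions attended.
4. Keep an all-source total for all randomised participants, so that the intention-to-treat basis is preserved and events in people who return no questionnaire still appear.
5. Continue to report all serious adverse events regardless of source.

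The cost is one source field on the form and one split in a table, with no extra data collection and no change to how events are reviewed for safety. The downside is that the comparative count omits events known only to sites, though these remain reported under items 3 and 4. Unequal questionnaire return, or unequal willingness to report between unblinded arms, would remain; showing the denominator makes unequal return visible.

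### The SAE definition requires an event to be unexpected and intervention-related as well as serious, which conflicts with the surrounding text and leaves some serious events outside the reported counts

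*Protocol article*

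**What the plan says.** All the relevant rules stand in the protocol article.

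- **Adverse events, scope of recording:** "Foreseeable adverse events (AE) occurring as a result of the trial intervention(s) will be recorded".
- **Adverse events, what is not recorded:** "Expected general side effects of any exercise, such as delayed-onset muscle soreness and temporary increases in pain <1 week, will not be recorded".
- **Adverse events, events named in advance:** after remarking that they are unlikely, the section says that "any exacerbations of other medical conditions during exercise or exercise-related injurious falls will be recorded in patient-reported questionnaires or by the site investigators", the latter if they come to know of one.
- **Adverse events, SAE definition:** "A serious AE (SAE) is any unexpected untoward medical occurrence related to the trial interventions that results in death, is life-threatening", continuing with "requires inpatient hospitalisation or prolongation of existing hospitalisation, or results in persistent or significant disability/incapacity".
- **Adverse events, handling:** for an SAE arising between enrolment and the final follow-up visit that "is deemed related to the trial interventions, the Clinical Trials Unit standard operating procedures will apply".
- **Statistical analysis:** "AEs, and SAEs will be reported, both the number of participants that experience an event and the total number".

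Elsewhere, Outcomes lists hospital admission among the health resource data taken from participant questionnaires, and Table 2 lists patient-reported adverse events at 3 and 6 months. Ethics and dissemination gives review of AEs and SAEs to the trial management group. No section gives a wider SAE definition.

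**The concern.** Seriousness describes the outcome of an event. Relatedness and expectedness are judgements made about the event afterwards, usually to decide how it is handled. When all three are conditions of entry, an event that fails either judgement drops out of the count. A reader of the results then cannot see that it happened or check the judgement.

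Two kinds of serious event are affected. One is the death or admission judged unrelated. The other is the serious event that the protocol itself foresaw. Injurious falls are the clearest example, in adults aged 50 and over doing balance and functional resistance work at home after an ankle fracture.

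This pilot exists to settle procedures for a definitive trial. A definition that leaves such events out could be carried forward, and a low SAE count could be taken as more reassuring than it is.

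**Working it through.** No formula applies and the plan gives no figure to reproduce. The check is to read the definition as a conjunction and test it against its neighbouring sentences.

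**Step 1. The rule.** SAE = serious outcome AND related AND unexpected. The scope sentence for AEs = foreseeable AND resulting from an intervention.

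**Step 2. Apply both rules to an event with a serious outcome.**

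| Related? | Foreseen? | AE under the scope sentence? | SAE? |
|---|---|---|---|
| Yes | No | Not clearly | Yes |
| Yes | Yes | Yes | Depends on whether a foreseen event can be *unexpected* |
| No | No | No | No |
| No | Yes | No | No |

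Of the four combinations, one is certainly counted as an SAE, one is uncertain, and two are excluded by the relatedness condition alone. The two exclusions do not depend on how *unexpected* is read.

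**Step 3. Test for consistency within the section.**

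- The handling sentence applies relatedness to something already called an SAE. Under the definition that condition is redundant. It does work only if unrelated SAEs can exist.
- The sentence between the definition and the handling rule says SAEs are unlikely to result from the exercise programmes. That too reads most naturally if some SAEs have other causes.
- The recorded AEs are described as foreseeable, while a serious AE must be unexpected. On a natural reading the two sets hardly overlap, although an SAE should be a kind of AE.

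**Step 4. Look for another route for the excluded events.** Admissions are collected at 3 and 6 months as resource use, by participant questionnaire. This depends on response. The retention criterion under Feasibility criteria is at least 80% at 6 months. With 48 participants it is met with 39 followed up (39/48 = 81.3%) but not with 38 (38/48 = 79.2%), so up to 48 − 39 = 9 could be missing with the criterion still satisfied. A participant who dies cannot return a questionnaire. Withdrawals are reported with reasons where provided, but that is not a safety count.

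**Step 5. Trace to the analysis.** The planned AE and SAE summaries use these categories, so whatever Step 2 excludes is absent from the reported numbers.

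**The case against.** The strongest reply is that the text is loose rather than exclusionary, and that little information is lost. Much of this is fair.

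- **A reader might infer that every serious fall is excluded.** The documents do not establish that. The word *expected* is attached only to muscle soreness and brief pain, and injurious falls are described as unlikely. A site could class a fall with admission as unexpected. The exclusion is one reading, and the fault is that the text leaves it open.
- **A reader might infer that the SAE count must come out near zero by construction.** That is not shown. Related, unforeseen serious events still count, and a pilot of 48 to 60 people may well see few SAEs under any definition.
- **A reader might infer that unblinded site staff decide what enters the count.** The article does not say who judges relatedness. It says only that the trial management group reviews AEs and SAEs.
- **A reader might infer much heavier reporting in the exercise arm because it has more sessions.** Six sessions is a ceiling and the programme may end early, while advice runs from one to three. Assuming at least one session attended, the ratio of contacts can lie anywhere from 1/3 to 6/1. Contacts are not reports, no reporting rate is given, and both arms receive the same questionnaires.
- **Other capture exists.** Injurious falls are recorded, admissions are collected, and Table 2 lists patient-reported adverse events without restricting them to foreseeable ones. Nor does the scope sentence say that nothing else is recorded. So it would be too strong to say that unforeseen non-serious events have no route at all.
- **The Clinical Trials Unit procedures are not shown and may be wider.**

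What remains is that the article fixes a definition, the definition conflicts with the sentences around it, and none of these other routes turns an unrelated death or admission into a counted SAE.

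**Conclusion.** The point holds as a defect of definition and internal consistency. Taken as written, serious events judged unrelated fall outside both the SAE definition and the stated scope of AE recording, so they do not reach the counts planned under Statistical analysis. This needs no assumption beyond reading the text literally. Serious events named in advance may be missing from the SAE count. That second part rests on reading a foreseen event as not unexpected, which is natural but not forced.

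The loss is mainly one of classification, handling and reporting, since injurious falls and admissions are partly captured elsewhere. It cannot be put as a number of events, because the documents give no event rates. None of the four success criteria concerns safety, and no test or stopping decision is stated to rest on the SAE count. It should be fixed, but it does not undermine the pilot's main feasibility conclusions.

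**What to change.** 1. Define an SAE by the seriousness criteria alone (death, threat to life, admission or its prolongation, lasting or significant disability). Keep the existing window from enrolment to the final follow-up visit.
2. Record relatedness and expectedness as two separate fields on the event form, and state who completes them.
3. Record AEs whether or not they were foreseeable. The stated exception for ordinary short-lived exercise effects can stay.
4. Reword the handling sentence so that relatedness, and expectedness if wanted, decides which SAEs go through the Clinical Trials Unit procedures, not which events are SAEs.
5. Under Statistical analysis, report SAEs by arm, overall and by relatedness, as participants and as events.

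The cost is a wording change, two extra fields and a few more unrelated events to log. Handling under the unit's procedures need not grow.
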